**Methods/Design:**

In this study, 90 patients with cancer receiving hospice or palliative care will complete a mixed-methods randomized controlled trial of Dignity Therapy (*n* = 45) versus Supportive Attention (*n* = 45). The patients will be enrolled in the study for 3 weeks, receiving a total of six study visits. The primary outcomes examine whether the treatment will quantitatively increase levels of positive affect and a sense of life closure. Secondary outcomes focus on gratitude, hope, life satisfaction, meaning in life, resilience, and self-efficacy. Using a fixed, embedded dataset design, this study will additionally use qualitative interviews to explore patients’ perceptions regarding the use of positive outcome measures and whether these outcomes are appropriately matched to their experiences in therapy.

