**Fig. 1 Fig1:**
[figure not shown]
Study flow-chart of the randomized controlled trial of Dignity Therapy focused on positive outcomes

All of the patients in the study will be followed for 14 days, with evaluations occurring at baseline and at the end of treatment. Each hour-long therapy session also includes the administration of two brief assessments related to positive affect and life satisfaction to explore whether each session provides some level of beneficial effect (please see Table 1 for a list of the study assessments and schedule). This study protocol and all accompanying materials have been approved by the University of California, San Diego Institutional Review Board and Human Research Protections Program.

**Table 1 Tab1:** Study outcomes and assessment schedule for the randomized controlled trial of Dignity Therapy focused on positive outcomes

Instrument	Time in minutes	Baseline	Session 1	Session 2	Session 3	Session 4	Post-Test
Positive and Negative Affect Scale (PANAS)	5	•	•	•	•	•	•
Life Closure Scale (LCS)	10	•					•
Hearth Hope Index (HHI)	5	•					•
Satisfaction with Life (BPFSS)	3	•	•	•	•	•	•
Gratitude Questionnaire (GQ-6)	5	•					•
Connor-Davidson Resilience Scale (CD-RISC)	7	•					•
Hospital Anxiety and Depression Scale (HADS)	5	•					•
Life Evaluation Questionnaire (LEQ)	10	•					•
Self-Efficacy (GSE)	5	•					•
Study Completion Questionnaire	5						•
	TOTAL	70	10	10	10	10	75

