### Statistical analyses

Descriptive statistics will be obtained for all variables, including distributions, means, medians, variances, standard deviations, skewness, kurtosis, ranges, and quartiles. Tests of normality of continuous measures will be made using the Shapiro-Wilk W and the Kolomogorov D statistics in conjunction with plots of the distribution of data and descriptive measurements. The data will also be examined for homogeneity of variance. An appropriate statistical method will be employed to correct for any abnormalities (such as log, square root, and inverse). All statistical tests will be two-tailed. Differences will be considered statistically significant provided a *p*-value ≤ 0.05 is obtained. The comparability of the two treatment groups in baseline demographic and clinical features will be tested with analyses of variance (ANOVAs) for continuous variables and Chi-square analyses for dichotomous variables.

Analyses will be based on a Random Regression Model (RRM) for continuous data using a generalized linear model [33, 34]. This model was selected over more traditional analytic approaches such as a change score, end-point, or repeated measures analysis of variance for several reasons. First, a 14–20 % death rate is anticipated based on pilot studies, and using this statistical method, we will be able to include all of the patients with missing data, early termination, or death without relying on data imputation procedures. Second, both fixed and time-varying covariates and systematic person-specific deviations from the average time trend are allowed in this method. A fully saturated treatment by time model will be utilized for inference. Co-variance structure will be chosen based on Akaikes Information Criterion (AIC). Random group level treatment effects will also be evaluated for importance based on the model AIC. This allows for any group level effects to be incorporated into the model. Denominator degrees of freedom will be calculated using the Kenward-Roger small sample correction.

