In order to assess how resilience and self-efficacy may mediate or moderate the impact of Dignity Therapy, we will use a RRM method similar to the primary hypotheses. The effect of mediator and moderator variables will be explored using RRM for each candidate mediator and moderator as a main effect and an interaction [35, 36]. If the interaction effect is significant, pairwise comparisons of groups will be performed. These analyses will examine interactions of treatment group with time at each level of the mediator and moderator, and evaluate treatment levels within each subgroup.

Finally, the time course of treatment of each individual will be modeled by projecting the outcome measures on orthogonal linear, and quadratic of time. Model diagnostics will be used to determine the suitability of an autoregressive error component and nonlinear effects for assessment time. Analyses will be performed using the SPSS (version 21.0) procedures. Data will be included for all patients completing at least one assessment after baseline.

The assumptions for sample size and power calculation are based on our pilot data and using procedures described by Hedeker et al. for Random Regression Models (RRM) [37]. With the proposed sample size of 86 subjects without attrition or 90 subjects adjusted for attrition (45 for each of the two groups), the study will have power of 80 % to yield a statistically significant result for a medium effect size. Here, medium effect size is defined as a between-group difference increasing linearity from 0 at baseline to 0.5 SD units at session 4. Results from this study will provide information regarding appropriate power calculations to further determine necessary effect sizes for larger-scale studies in the future.

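### The primary Life Closure Scale has only two measurements, so the planned model is essentially a change-score test and the stated 80 % power is unsupported for it

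*Protocol article*

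**What the plan says.** The abstract of the Protocol article (Methods/Design) names two primary outcomes: "The primary outcomes examine whether the treatment will quantitatively increase levels of positive affect and a sense of life closure". Table 1 marks the PANAS at all six occasions (baseline, sessions 1 to 4, post-test). It marks the LCS at baseline and post-test only. The text above the table agrees: "Each hour-long therapy session also includes the administration of two brief assessments related to positive affect and life satisfaction". Six secondary instruments follow the same two-visit schedule as the LCS: HHI, GQ-6, CD-RISC, HADS, LEQ and GSE.

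Under Statistical analyses, one model serves every continuous outcome: "Analyses will be based on a Random Regression Model (RRM) for continuous data using a generalized linear model". For the mean structure, "A fully saturated treatment by time model will be utilized for inference". The choice is explained thus: "This model was selected over more traditional analytic approaches such as a change score, end-point, or repeated measures analysis of variance". Two reasons follow. The model keeps patients with missing data or death (14–20 % deaths are expected) without imputation, and it allows person-specific deviations from the time trend. The section later adds linear and quadratic time components for each individual and a diagnostic check for an autoregressive error. Patients with at least one assessment after baseline are included.

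The only power statement gives 80 % with 86 patients (90 after adjustment for attrition), where "medium effect size is defined as a between-group difference increasing linearity from 0 at baseline to 0.5 SD units at session 4".

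**The concern.** The rationale for the model and the power statement are both written for an outcome measured repeatedly through session 4. That describes the PANAS but not the LCS. For the LCS, the model chosen in preference to a change score turns into one, the two reasons given for it have almost no force, and the effect that defines the power refers to a visit at which the scale is not administered.

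Two things are at stake. A null LCS result would be read against an 80 % power that the article never derives for that outcome. And the collected baseline LCS score would not be used to gain the precision that it offers at no cost.

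**Working it through.** **1. The plan's own figure.** The article gives no within-patient correlation, so 86 can be neither confirmed nor refuted. It is reachable. Take five equally spaced points (baseline to session 4), compound symmetry with correlation r, a linear rise of 0.125 SD per step, and centred linear scores c = (−2, −1, 0, 1, 2). The variance term is c′Vc = 10(1 − r) and the signal is c′d = 10 × 0.125 = 1.25. Then

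n per arm = 2(1.96 + 0.84)² × 10(1 − r) / 1.25².

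At r = 0.572 this is 15.70 × 4.28 / 1.5625 = 43.0, or 86 in total. An end-point comparison of 0.5 SD with no use of baseline needs 63 per arm (126 in total). The stated 86 therefore depends on repeated or correlated measurements.

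**2. What the model becomes with two occasions.** With free baseline means in each arm, the treatment-by-time term is (post − baseline) in one arm minus (post − baseline) in the other. A simulated data set with 45 per arm confirms this:

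| Data used | Mixed model, estimate (t) | Change score, estimate (t) |
|---|---|---|
| All pairs complete | 0.5751 (3.707) | 0.5751 (3.707) |
| 22 of 90 post-tests missing, their baselines kept | 0.5120 (2.868) | 0.5134 (2.821) |
| Same, baseline-only patients excluded | 0.5134 (2.821) | 0.5134 (2.821) |

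So the identity is exact for complete pairs, and very close otherwise. With two points, a random slope cannot be separated from residual error, a quadratic term cannot be fitted, and an autoregressive error cannot be told apart from compound symmetry.

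**3. Power for the LCS.** Inputs: 43 per arm (86/2), two-sided 0.05, equal variances at both visits. Assumptions: r between baseline and post-test, and the post-test difference. The article places 0.5 SD at session 4, and post-test is the next column of Table 1. The difference may therefore stay at 0.5 SD or, if the ramp continues by one more equal step, reach 0.5 + 0.125 = 0.625 SD. The SD of change is √(2(1 − r)) and that of a baseline-adjusted outcome is √(1 − r²). Power is from the noncentral t on 84 degrees of freedom.

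| r | Change score, 0.5 SD | Change score, 0.625 SD | Baseline-adjusted, 0.5 SD |
|---|---|---|---|
| 0.3 | 49 % | 68 % | 67 % |
| 0.5 | 63 % | 82 % | 75 % |
| 0.57 | 70 % | 87 % | 80 % |
| 0.7 | 84 % | 96 % | 89 % |
| 0.8 | 95 % | over 99 % | 97 % |

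For 0.5 SD, the change-score test reaches 80 % only at r of about 0.67 or more. At r = 0.572, where the five-point slope needs 86 patients, the two-point change needs 2 × 7.85 × 2(1 − 0.572)/0.25 = 53.8, so 54 per arm or 108 in total.

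**4. Precision left unused.** The variance ratio of the baseline-adjusted to the change-score estimate is (1 − r²)/(2(1 − r)) = (1 + r)/2. That is 0.75 at r = 0.5, 0.785 at r = 0.57 and 0.85 at r = 0.7, a reduction of 25 %, about 21 % and 15 %.

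**The case against.** **A reader might infer that the LCS is underpowered.** The documents do not show that. They give neither r nor a post-test effect, and the table above holds values on both sides of 80 %.

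**A reader might infer that the LCS test is wrong.** It is not. A change-score comparison is valid under randomisation. The article prefers its model to a change score without calling the latter invalid, and it permits covariates, so baseline adjustment is not excluded.

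**A reader might infer that the missing-data benefit is absent, or that the extra model terms make the analysis fail.** Both go too far. If the inclusion rule is read per patient, someone with a session PANAS but no post-test keeps a baseline LCS in the likelihood, which brings a small gain. Only if the rule is read per outcome is the reduction to a change score complete, and the article does not settle which is meant. A first-order autoregressive correlation can be estimated from two occasions; it is simply the same single parameter as compound symmetry. Covariance is to be chosen by AIC, and the autoregressive and nonlinear terms are subject to diagnostics. Only the quadratic projection is stated without such a condition.

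**Attrition is a separate matter.** Going from 86 to 90 allows 4/90 = 4.4 % loss against 14–20 % expected deaths. That bears on the LCS, because a missed post-test leaves no follow-up value, but the two-visit schedule does not cause it. The power figures here therefore use 43 per arm.

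It is also fair to say that outcome-specific model detail often sits in a fuller plan, and that the article presents its results as informing power for larger studies. What remains is that the article itself fixes one model, one rationale and one power definition for both primary outcomes, and two of these, the rationale and the power definition, do not fit the LCS.

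**Conclusion.** The point holds in this form. For the LCS, the saturated treatment-by-time model is essentially a change-score comparison, exactly so for complete pairs. The stated advantages of the model bring almost nothing for this outcome. The test is valid but less precise than a baseline-adjusted one, by 15–25 % in variance for r from 0.7 to 0.5. The 80 % power is unsupported for the LCS because its defining effect ends at a visit where the scale is not taken. Whether the true figure lies above or below 80 % cannot be decided from the article, since it turns on two unstated quantities, r and the post-test difference.

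**What to change.** 1. For the LCS and the six other instruments taken only at baseline and post-test, use the treatment-by-time model with baseline means constrained equal across arms. ANCOVA of post-test on baseline is nearly the same, but it drops patients who have a baseline value only.
2. Confine quadratic time, random slopes and autoregressive errors to the outcomes measured at every session, namely the PANAS and the life satisfaction item.
3. Either state that the 80 % power applies to the PANAS only, or add an LCS power figure together with its assumed baseline-to-post-test correlation and post-test effect.

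The cost is analysis wording and one power line, and possibly a less favourable stated power for the LCS. No new data or patients are needed.

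### For PANAS Positive Affect, power rests on a linear divergence, but inference uses a saturated treatment-by-time model with no test tied to that trend; an omnibus interaction test would probably fall short of 80%

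*Protocol article*

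**What the plan says.** All of this is in the protocol article.

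- **Inference model** (Statistical analyses): "A fully saturated treatment by time model will be utilized for inference". The covariance structure is to be chosen by AIC. Linear and quadratic time appear only later, in a separate closing analysis of individual time courses.
- **Power basis** (same section): "the study will have power of 80 % to yield a statistically significant result for a medium effect size", where "medium effect size is defined as a between-group difference increasing linearity from 0 at baseline to 0.5 SD units at session 4". The sample is 86 without attrition and 90 with it, 45 per group. The method is described only as follows: "The assumptions for sample size and power calculation are based on our pilot data and using procedures described by Hedeker et al". No within-person correlation is given.
- **Significance**: "All statistical tests will be two-tailed", and "Differences will be considered statistically significant provided a *p*-value ≤ 0.05 is obtained".
- **Occasions** (Table 1): PANAS is taken at baseline, at sessions 1 to 4 and at post-test. The Life Closure Scale (LCS) is taken at baseline and post-test only. The text describes follow-up "with evaluations occurring at baseline and at the end of treatment", and Table 1 shows the post-test as a column separate from session 4.

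**The concern.** A difference that grows in a straight line is most naturally tested with one degree of freedom, as a difference in slopes. A saturated model has no slope parameter. Its overall treatment-by-time test has 5 df for PANAS over six occasions, or 4 df if it stops at session 4. An omnibus test spreads the same signal over more degrees of freedom, so it has less power against a straight-line pattern.

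The omnibus reading is a natural one. The mediator and moderator analyses are described as similar to those for the primary hypotheses, and there the interaction is tested first and pairwise comparisons follow if it is significant.

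The powered effect is also fixed at session 4, while the end-of-treatment evaluation is the post-test. A reader therefore cannot tell which PANAS test the 80% refers to. With 43 to 45 patients per arm there is little power to spare.

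**Working it through.** **Inputs from the article:** two-sided alpha 0.05; 80% power; 43 per arm (86/2) before attrition; differences of 0, 0.125, 0.25, 0.375 and 0.5 SD at baseline and sessions 1 to 4. **Assumed:** equally spaced occasions, equal variances, and a within-person correlation ρ, which the article does not give.

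**1. Can the stated 80% be reproduced?** Not from the printed inputs alone.
- A plain comparison of 0.5 SD at one time point gives √(43/2) × 0.5 = 2.32, and Φ(2.32 − 1.96) = 64%. The 80% must therefore draw on the repeated measures.
- For a linear contrast c = (−2, −1, 0, 1, 2), c′δ = −0.125 + 0.375 + 1.0 = 1.25. Under compound symmetry c′Σc = 10(1 − ρ), so the noncentrality is λ = 1.25² / [(2/43) × 10(1 − ρ)] = 3.36/(1 − ρ).
- 80% power needs λ = (1.960 + 0.842)² = 7.85, hence ρ = 0.57. Under AR(1) the value is 0.91.

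**2. Omnibus interaction, baseline to session 4 (4 df).** Under compound symmetry λ = 43/[2(1 − ρ)] × Σ(δₜ − δ̄)². The sum of squares is 0.15625, so λ = 6.72/0.856 = 7.85. This is the same noncentrality, now tested on 4 df.
- The noncentral chi-square gives 59.5%, and the F version 58.8%.
- AR(1) gives 61.8% and 61.1%.
- At 45 per arm the range is 61–64%.

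**3. With the post-test (5 df), 43 per arm, chi-square.** The article does not say what the difference does after session 4. Two shapes were used: it stays at 0.5 SD (plateau) or grows on to 0.625 SD.

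| Waves and shape | Covariance | Linear, 1 df | Omnibus |
|---|---|---|---|
| 5 | CS 0.57 | 80% | 60% |
| 5 | AR(1) 0.91 | 80% | 62% |
| 6, growing | CS 0.25 | 80% | 56% |
| 6, growing | AR(1) 0.87 | 80% | 59% |
| 6, plateau | CS 0.45 | 80% | 57% |
| 6, plateau | AR(1) 0.91 | 80% | 61% |
| 6, plateau | CS 0.57 (from five waves) | 89% | 70% |
| 6, growing | CS 0.57 (from five waves) | 96% | 83% |

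In the first six rows ρ is set so that the linear test has 80%. The F version brings the lowest six-wave figure to 55%.

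**4. Does the gap depend on the calibration?** Over five waves under compound symmetry, linear against omnibus power is 59% vs 38% at ρ = 0.3, 74% vs 52% at 0.5, 83% vs 63% at 0.6 and 92% vs 77% at 0.7. The gap is 15 to 22 points throughout.

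**5. Other tests a sponsor might choose.** The baseline-to-post-test contrast at CS 0.57 with a plateau has 71% power with free baseline means, and 81% with adjustment for baseline. Giving the omnibus test 80% would take about 64–66 per arm (4 df) or 64–71 (5 df).

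**6. LCS.** With two occasions the saturated interaction has 1 df, so there is no omnibus penalty.

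All figures are before attrition.

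**The case against.** The strongest reply is that a saturated model is a choice of mean structure and not of test. A 1-df linear contrast can be taken from it, and under compound symmetry that contrast keeps the stated power. The article never says that the omnibus interaction is the primary test. This stands, and it makes every omnibus figure conditional.

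It can also be said that the 1-df basis of the 80% is inferred from the shape of the effect, that the correlation is solved backwards, and that higher correlations shrink the gap. That is also right. Calibrating to 80% accepts the sponsor's own figure, and the order of the two tests did not change at any correlation checked.

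The last reply is that a journal article may leave the primary contrast to the analysis plan. That would dispose of a bare omission. Here the article states both an inference model and a power basis, and places linear time only in a separate closing analysis, so the two printed statements do not connect.

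Two stronger readings are tempting, and the document supports neither:
- **The trial has 60% power, not 80%.** This requires the omnibus test, the 1-df basis and the back-solved correlation all to hold, and it drops the sixth PANAS wave. Keeping that wave at the same correlation gives 70–83%.
- **Visit contrasts will be picked after the data are seen.** Nothing in the article says so.

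**Conclusion.** The mismatch is real and limited to PANAS Positive Affect. The power statement describes a linear divergence to session 4, inference is tied to a saturated model, and no test links them.

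The size depends on the test. If it is the omnibus interaction, and the 80% belongs to a 1-df linear test, the loss is about 18 to 21 points over baseline to session 4 at 43 per arm. With the post-test it is 19 to 25 points if the 80% is calibrated on six waves. At the five-wave correlation of 0.57, omnibus power lies between 10 points below 80% and 3 points above it.

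If the linear contrast is the intended test, nothing is lost under compound symmetry and only the wording needs repair. The article does not allow a choice between these cases. What does not depend on that choice is that, for the effect the sponsor powered, the linear contrast was the more powerful test in every compound-symmetry case checked.

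**What to change.** Keep the saturated mean model. Add one sentence naming the 1-df linear treatment-by-time contrast from that model as the primary test for PANAS Positive Affect, and stating whether it runs to session 4 or to the post-test. Report the omnibus interaction and the visit contrasts as supportive. If the sponsor prefers the omnibus test or the post-test difference, restate the power for that test. In either case, give the within-person correlation and covariance structure behind the 80%.

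The cost is a sentence or two, with no change to the design or to data collection. The downside is that a linear contrast is less sensitive to an effect that appears only late; the supportive contrasts would show such a pattern. The LCS test needs no change on this account.

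### The saturated treatment-by-time model leaves the baseline arm difference free, although randomisation and the power assumption put it at 0; a common baseline mean would gain precision at no cost, by an amount the documents do not fix

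*Protocol article*

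**What the plan says.** The Statistical analyses section of the protocol article names the model for the treatment comparison: "A fully saturated treatment by time model will be utilized for inference". It leaves the covariance structure to AIC, applies the Kenward-Roger correction, and counts individual departures from the mean time trend among the reasons for choosing the method. It says that covariates can be accommodated, but it commits to neither a baseline covariate nor a common baseline mean. "All statistical tests will be two-tailed", at the 0.05 level.

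Table 1 lists the PANAS, one of the two primary measures, at baseline, at each of sessions 1 to 4 and at post-test. The Life Closure Scale is listed at baseline and post-test only.

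The power statement claims 80% "to yield a statistically significant result for a medium effect size", defined as "a between-group difference increasing linearity from 0 at baseline to 0.5 SD units at session 4". The numbers behind it are 86 patients before attrition and 90 after.

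The text under Exclusion criteria places random assignment after informed consent. It does not say whether the baseline assessment comes before or after that assignment.

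**The concern.** A saturated treatment-by-time model has a separate mean for each arm at each occasion. The power statement starts the effect at baseline, so baseline is naturally read as one of those occasions. The model then estimates a baseline arm difference, and the treatment effect becomes a departure from that estimate: a difference in change or in slope.

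In a randomised trial the baseline difference is 0 in expectation, and the plan's own effect definition also puts it at 0. Estimating it carries the chance imbalance at baseline into the treatment contrast. The baseline scores could instead be used to remove that noise.

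What is at stake is precision in a small trial that claims no more than 80% power. Validity is not at stake.

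**Working it through.** **Inputs from the article.** Two-sided 0.05; 86 patients without attrition, so n = 43 per arm; arm difference rising linearly from 0 at baseline to 0.5 SD at session 4, so d = (0, 0.125, 0.25, 0.375, 0.5) over five occasions.

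**Not given, so assumed.** The within-patient correlation, the covariance structure and the exact test. I use the linear treatment-by-time contrast c = (−2, −1, 0, 1, 2) and a normal approximation.

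**Step 1. The stated 80%.** A comparison at session 4 alone gives 0.5/√(2/43) = 2.32, and Φ(2.32 − 1.96) = 64%, so it does not reproduce the figure. For the linear contrast, c′d = −0.125 + 0.375 + 1.0 = 1.25. With compound symmetry and correlation ρ,

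Var(free baseline) = (2/n) × 10(1 − ρ).

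At n = 43, 80% power requires ρ = 0.572: 10 × 0.428 = 4.28; SE = √(2 × 4.28/43) = 0.446; 1.25/0.446 = 2.80; Φ(2.80 − 1.96) = 80%. Because ρ was solved for, this is a calibration and not an independent reproduction.

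**Step 2. Fix the baseline difference at 0 and leave later visits saturated.** Write Σ for the covariance of one patient's five scores and e₀ for the baseline position. Conditioning on baseline gives

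Var(constrained) = (2/n) × [c′Σc − (c′Σe₀)²/Σ₀₀].

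The subtracted term cannot be negative, so for a given covariance the variance never rises. Under compound symmetry c′Σe₀ = −2(1 − ρ) and Σ₀₀ = 1, so the variance ratio is 1 − 0.4(1 − ρ).

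| ρ | c′Σc, free | constrained | ratio | power, free | power, constrained |
|---|---|---|---|---|---|
| 0.3 | 7.00 | 5.04 | 0.72 | 59% | 73% |
| 0.5 | 5.00 | 4.00 | 0.80 | 74% | 83% |
| 0.572 | 4.28 | 3.55 | 0.83 | 80% | 87% |
| 0.7 | 3.00 | 2.64 | 0.88 | 92% | 95% |

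**Step 3. Random slopes.** Take intercept variance r₀, residual variance 1 − r₀, slope variance s (SD² per visit²) and no intercept-slope covariance. Then c′Σc = 10(1 − r₀) + 100s, and c′Σe₀ is still −2(1 − r₀). For each s, r₀ is set so that c′Σc = 4.28, which keeps the free-baseline power at 80%.

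| s | r₀ | 4(1 − r₀)² | ratio | power, constrained |
|---|---|---|---|---|
| 0.005 | 0.622 | 0.572 | 0.866 | 85.3% |
| 0.01 | 0.672 | 0.430 | 0.899 | 84.0% |
| 0.02 | 0.772 | 0.208 | 0.951 | 81.9% |
| 0.03 | 0.872 | 0.066 | 0.985 | 80.6% |

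The more of the variation in trends that lies between patients, the less the baseline score can remove.

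**Step 4. Other readings of the test.** With ρ = 0.572 and 43 per arm, the change from baseline to session 4 goes from 71% to 81%, and the four-degree-of-freedom omnibus interaction from about 60% to 71%. With an AR(1) structure at 0.9 per step, the linear contrast goes from 78% to 85%. The direction is the same in every case; the level is not.

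**The case against.** The strongest reply is that nothing here is wrong. The saturated model is a standard analysis, unbiased and with correct type I error. A planning assumption of 0 at baseline does not contradict a model that leaves the parameter free. That stands, and it is why the point is one of efficiency only.

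A second reply is that a journal article condenses the plan. It allows covariates, and its rule of including patients with at least one post-baseline assessment would also suit a baseline-covariate model. This is possible. But the article does commit itself to a saturated model for inference, and its power statement treats baseline as the start of the time course, so the point rests on stated text.

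Three stronger readings are tempting, and the documents do not support them.

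- A reader might infer that about a fifth of the precision is lost and that the same patients would give 88%. Those figures (variance 21% lower, power 88.2%) need compound symmetry, a correlation near 0.57 and an arm difference forced to be linear through 0. The last is a shape assumption that a common baseline mean does not make.
- A reader might infer that the gain outweighs what the expected 14% to 20% deaths cost. With random slopes, which the method expressly allows, the gain can be under one percentage point, so this cannot be claimed.
- A reader might infer that the constraint can never introduce bias. It requires that allocation cannot have affected the baseline scores, and the text does not give the order of assessment and randomisation.

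**Conclusion.** The point holds as a free improvement of uncertain size. The stated model, with baseline as a time point, estimates a difference that randomisation and the plan's own effect definition put at 0, and this costs precision when treatment by time is tested.

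Starting from the stated 80%, fixing only the baseline difference gives about 87% under compound symmetry and about 81% to 85% over the random-slope cases in step 3. These figures rest on 43 evaluable patients per arm, five occasions, a linear contrast and an assumed covariance. If the test is the omnibus interaction, neither the 80% nor the 87% applies. The 80% is itself the article's figure for 86 evaluable patients out of 90, a loss of 4/90 = 4.4%, so the starting level would also move with the expected deaths.

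**What to change.** In the Statistical analyses section, replace the sentence on the saturated model with one specifying visit effects, and treatment-by-visit effects at post-baseline visits only, so that both arms share one baseline mean. Essentially the same result comes from modelling the post-baseline visits with the baseline score as a covariate, its effect allowed to differ by visit. Apply this to the PANAS and to every other scale with a baseline value. The AIC covariance choice and the Kenward-Roger correction can stay as planned.

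The sponsor should first confirm, and the text should state, that the baseline assessment is completed before allocation is known. The same sentence should name the contrast to be tested, and the power statement should give the correlation and covariance assumed.

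The cost is a few sentences. No further patients, visits or data are needed, because the baseline scores are already collected.
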